### Risk management and safety

Though the study is not associated with any physical risk to mentees or mentors, potential psychological risk exists through participation in the program. If mentees experience distress at any time during the program, they will be advised to contact the EDV Project Coordinator or the research team as soon as possible. The research team will determine the suitability for continuing the participant with the program and will contact emergency services and/or provide information related to psychological support available, as appropriate.

Mentors will have their own Wellness Plan that outlines their current supports and contact details in case of emergency. Mentors will also complete an online survey following each session with the participant, which has facility to request a support call from the EDV team. Mentors and mentees can also contact the project coordinator or psychologist any time for individual support, and they will attend three group debriefing sessions throughout the program. There are guidelines in place to manage self-reported increased eating disorder symptoms/risk for mentees which include referring mentees back to their treating clinician for assessment and support.

All data will be securely stored via password protection (electronic data) and under lock-and-key (hard copy data) at EDV in the short term, prior to long-term storage at St Vincent’s Hospital.

### Handling of withdrawals and replacements

Participants (mentees or mentors) are free to withdraw from the study without explanation. Data collected will be retained, unless otherwise specified by the participant. If agreed by the participant, they will also be afforded the opportunity to complete relevant follow-up assessments.

If a mentee or a mentor withdraws from the program, replacement participants will be sought. This will ensure that mentees will not be significantly affected by their partner’s (mentor) withdrawal and that the study has sufficient statistical power to identify efficacy of the program. Debriefing will be offered by program staff to the remaining participant, and mentees will be re-matched with another suitable mentor.

## Statistical methods

### Sample size estimation and justification

Thirty mentors and a minimum of 30 mentees will be recruited. This minimum sample size of 60 participants will enable differences to be identified between time points in a pilot evaluation (i.e. 28 participants per group will enable the identification of a moderate effect size with power of 0.8 and alpha of 0.05 for a within-group analysis between baseline and the primary endpoint). Sample size has been determined using the qualitative principle of data saturation, which provides an estimate of sample size based upon the comprehensiveness of the data set to identify all of the issues affecting the population under study. As Fusch and Ness [37] highlight, data saturation is the point when (a) no new insights related to the research aims and objectives are gained from additional interviews or through further analysis and (b) there is sufficient information gathered for the study to be replicated. The proposed participant numbers of 60 or more participants (30 per group) is deemed be sufficient to capture the variance in information that occurs within each participant group. Guest and colleagues [38] argue that data saturation occurs after as few as six interviews, with all information (themes) fully elucidated after 12 interviews. Our prior clinical-based qualitative research [39–41] indicates that this varies considerably based on the population under study but typically occurs after 7 and 14 interviews. Given the variability in the present sample by age, gender and anything else, our planned sample will be sufficient to gather powerful information on our study aims and objectives.

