### Primary hypotheses

Participation in the peer mentor program is hypothesised to improve eating disorder symptomatology and quality of life, and reduce relapse rates in eating disorder participants (i.e. ‘mentees’, also referred to as ‘participants’ in appendices).

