## Methods/design

### Study design and mentor-mentee matching

The study is a multi-site collaborative trial conducted at Eating Disorders Victoria (EDV), The Melbourne Clinic (TMC),  and the Body Image and Eating Disorders Treatment and Recovery Service (BETRS) at the Austin Hospital (inpatient unit) and St Vincent’s Hospital (intensive day patient program), all in Melbourne, Victoria, Australia. Up to 30 mentees with an eating disorder (anorexia nervosa, bulimia nervosa, binge eating disorder or eating disorder not otherwise specified, according to the Diagnostic and Statistical Manual of Mental Disorders 5) will be matched with up to 30 mentors with a past history of an eating disorder. Participation will involve a longitudinal study assessing the efficacy of a peer mentor program for individuals with eating disorders. All mentees and mentors will be over the age of 18 years.

As this is a pilot proof-of-concept feasibility study, a randomised controlled trial will not be undertaken, but the program will be evaluated with a within-group design. Participation will involve a series of 13 mentoring sessions of up to 3 h each (ideally, every 2 weeks) over 6 months, following the mentee’s discharge from the BETRS/TMC inpatient unit or transition to/from the BETRS/TMC intensive eating disorders day program. The peer mentoring program will be delivered in a variety of community settings, i.e. local shopping centres, parks and cafes. Mentees and mentors will not be permitted to meet in either person’s home.

Mentors will be employed as ‘casual’ employees of EDV (see Additional file 1: Appendix A) and will be reimbursed for any reasonable expenses incurred during mentoring sessions as part of their employment, i.e. lunch for mentee and mentor, public transport fares for mentee and mentor practicing independent use of public transport, etc. Mentors and mentees will not receive any payment or reimbursement for this research.

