##### Qualitative interviews and feasibility

Given the limitations of the existing literature, the explorative nature and the qualitative research methodology of the current investigation, a broad semi-structured interview schedule will be used on completion of the program. This will be revised iteratively throughout the study to enable exploration of new themes raised by participants (mentors and mentees) and enable detailed exploration of the most important and relevant themes associated with participating in this program. The qualitative interviews will also cover areas A–C (see Additional file 1: Appendix F). The number of mentoring sessions completed and the participants’ capability to complete the mentoring sessions will also be assessed through the qualitative interviews.

Feasibility of the program will be guided by the CONSORT statement regarding assessing feasibility of trials [36]. Specifically, feasibility will be measured in terms of achieving sufficient numbers of participants signing up, participating and being retained in the program through the qualitative interview and records kept by mentors regarding program participation. The study will be deemed feasible if 80% of participants are able to complete the program and the target sample size is achieved within 2 years. Feasibility will also be measured in terms of tolerance and acceptance of the intervention, that the intervention can be delivered as per the protocol and identifying any adverse events related to the study through the qualitative interview and the participant feedback questionnaires. Any serious adverse events will result in the intervention not continuing to an RCT.

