## Discussion

Eating disorders are disabling and often long-term conditions. The efficacy of available treatments is limited, resulting in high relapse rates and significant morbidity and mortality. The current trial aims to assess the efficacy and feasibility of a peer mentor program (as a supplement to standard treatment) for patients with eating disorders, in terms of improvements in both eating disorder symptomatology and quality of life, as well as relapse rates. A unique aspect of this research is to assess the impact of this program on mentors to identify the positive and/or negative impact that engaging with current eating disorder patients has on someone who has recovered from an eating disorder. This study will assess any adverse effects on mentees or mentors and glean information that will inform refinement of the intervention for a full-scale randomised controlled trial. The findings of this pilot program will inform larger randomised controlled trials assessing the efficacy of peer mentoring for individuals with eating disorders, by providing preliminary data on the need of the program (i.e. participant flow and retention rate, and the magnitude of the outcomes to be clinically significant).

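### On the conventional reading, 28 per group gives about 72% power, not 80%, for the baseline-to-endpoint comparison named; 28 is reached only with settings the sentence does not state

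*Protocol article*

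**What the plan says.** Under *Sample size estimation and justification*, the protocol article plans 30 mentors and at least 30 mentees and states that "28 participants per group will enable the identification of a moderate effect size with power of 0.8 and alpha of 0.05". The same sentence says what the power is for: "for a within-group analysis between baseline and the primary endpoint". That is one group at two occasions. The effect is described only as moderate. No number, metric (SD of the change or SD of the raw score), within-person correlation, sidedness or named test goes with it.

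Four other places bear on the point:
- *Statistical methods* plans within-group ANOVAs and non-parametric tests between time points, separately for mentees and mentors, with multiple imputation for missing data.
- *Program evaluation* sets measurements at baseline, 3, 6 and 12 months, three of them within the program.
- *Qualitative interviews and feasibility* sets a completion threshold: "The study will be deemed feasible if 80% of participants are able to complete the program".
- *Handling of withdrawals and replacements* says replacements will be sought, partly to protect power, and offers follow-up assessments to those who withdraw and agree.

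**The concern.** A statistician who reads a moderate effect as a standardised mean change of 0.5, and tests baseline against one later time point with a two-sided paired test, will not get 28. The number needed is 34, and even the planned 30 falls short of 80%. The figure 28 does match a different analysis, a repeated-measures ANOVA over three occasions, which is not the comparison the sentence names.

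Evaluating the program's effect on mentee outcomes is stated as the primary aim, the withdrawal section relies on adequate power for efficacy, and the results are meant to inform later randomised trials. If true power is about 72%, a real change of 0.5 would be missed about 28% of the time instead of the advertised 20%. A reader who trusts the 80% could then take a null result as stronger evidence against a moderate change than it is.

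**Working it through.** **Inputs from the protocol:** alpha 0.05, target power 0.80, 28 per group (30 recruited), one group, two occasions. **Assumed, because not stated:** moderate means 0.5 (f = 0.25 for ANOVA); two-sided unless noted; correlation 0.5, with range 0.3 to 0.7.

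**1. Reproducing 28.** Repeated-measures ANOVA with m occasions, under sphericity: noncentrality λ = f²·n·m/(1 − r), on m − 1 and (n − 1)(m − 1) degrees of freedom.
- m = 3, r = 0.5, n = 28: λ = 0.0625 × 28 × 3/0.5 = 10.5, df 2 and 54, power 81.2%. With n = 27 it is 79.6%, so the required n is exactly 28.
- m = 4, r = 0.4, n = 28: λ = 0.0625 × 28 × 4/0.6 = 11.67, power 80.8%. The required n is again 28.

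Other routes to 28 or close to it:
- One-sided paired t-test, standardised change 0.5: required n is 27 (81.2%); power with 28 is 82.5%.
- One-sided signed-rank test (efficiency 3/π): 79.5% with 27 and 80.8% with 28, so 28.
- Two-sided paired t-test, 0.5 raw SD, r = 0.6: required n is 28 (81.4%).

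**2. The comparison named, on the conventional reading.** Two-sided paired t-test: noncentrality δ = dz·√n on n − 1 degrees of freedom; power is the probability that a noncentral t exceeds the two-sided 5% critical value in absolute size. With dz = 0.5:

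| n | δ = 0.5·√n | critical t | power |
|---|---|---|---|
| 28 | 2.646 | 2.052 | 72.3% |
| 30 | 2.739 | 2.045 | 75.4% |
| 33 | 2.872 | 2.037 | 79.5% |
| 34 | 2.915 | 2.035 | 80.8% |

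The two-occasion ANOVA (f = 0.25, r = 0.5) gives the same answer: λ = 0.0625 × 28 × 2/0.5 = 7.0 = 2.646², power 72.3%.

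**3. Change detectable with 80% power.** Solving the same formula for dz gives 0.55 with 28 and 0.53 with 30.

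**4. If the effect is 0.5 in raw-SD units.** Then dz = 0.5/√(2(1 − r)). Two-sided, two occasions:

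| r | dz | power, n = 28 | n for 80% |
|---|---|---|---|
| 0.3 | 0.423 | 57.8% | 46 |
| 0.4 | 0.456 | 64.4% | 40 |
| 0.5 | 0.500 | 72.3% | 34 |
| 0.6 | 0.559 | 81.4% | 28 |
| 0.7 | 0.645 | 90.9% | 21 |

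**5. Complete-case scenario.** Completion at the feasibility threshold gives 0.8 × 30 = 24. With dz = 0.5 and n = 24, δ = 2.449, the critical value is 2.069 and power is 65.0%; the detectable change is 0.60.

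**The case against.** The strongest reply is that 72% also rests on inputs the protocol does not give. A journal article may leave effect metric, correlation and sidedness to the full document, and the same two-point, two-sided comparison reaches 81.4% with 28 if moderate means 0.5 raw SD with correlation 0.6. This stands. A reader might infer that the 80% is simply an arithmetic error; the document does not support that, because it does not fix the inputs that would prove it.

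A second reply is that the three-occasion ANOVA belongs to the planned family of analyses and fits the three in-program measurements, so the sentence may only describe the powered test loosely. That is possible, but the sentence names baseline against the primary endpoint, and that the ANOVA was the source of 28 is an inference.

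One-sided testing is a weaker defence. The mentee hypothesis is directional ("Participation in the peer mentor program is hypothesised to improve eating disorder symptomatology and quality of life"), but the ANOVA F test is not, and for mentors, to whom the 28 also applies, the Discussion seeks to "identify the positive and/or negative impact that engaging with current eating disorder patients has".

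A reader might also infer that power falls to 65% at the completion rate the plan accepts, or that only two losses can be borne. Neither follows. The 80% threshold concerns finishing the program, not having outcome data; replacements are to be sought, those who withdraw may still be followed up, and missing data are imputed. The safeguards are not complete: replacement is only sought, follow-up needs agreement, and imputation does not restore all lost information. *Study design and mentor-mentee matching* also gives 30 as a ceiling ("Up to 30 mentees with an eating disorder") where the sample size section makes it a minimum. Even so, 24 is a complete-case scenario, not the expected analysis set.

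Finally, this is an uncontrolled pilot whose size is also justified by data saturation, and its feasibility criteria involve no significance test. That lowers the stakes but does not make the stated power right for the comparison named.

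**Conclusion.** The point holds in conditional form. For a two-sided paired test, or a two-occasion within-group ANOVA with correlation 0.5, and a standardised mean change of 0.5, the shortfall is about 8 percentage points with 28 (72% against 80%) and about 5 with 30 (75%), or six people per group (34 against 28). Put as an effect, the design detects a change of 0.55 where the usual meaning of moderate is 0.50.

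The size depends on reading moderate as 0.5 SD of the change. On the raw-SD scale, the unstated correlation alone moves power with 28 between 58% and 91%. What can be said firmly is that the sentence pairs a power figure with a comparison for which the usual calculation does not give it, and leaves out the settings under which it would. The discrepancy is modest and calls for a corrected statement, not a larger study.

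**What to change.** Keep the sample size and restate the figure for the comparison named, for example:

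> With 28 evaluable participants in a group, a two-sided paired comparison of baseline with the primary endpoint has 80% power for a standardised mean change (mean change divided by the SD of the change) of 0.55 (0.53 with 30). Power for a change of 0.5 is about 72% (75% with 30).

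The sample size section does not say which time point is the primary endpoint, so the restated sentence should not assume one.

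Alternatively, if the three-occasion ANOVA was the test powered, name it in place of the baseline-to-endpoint comparison, with its effect size (f = 0.25) and assumed correlation (0.5). If 0.5 raw SD with correlation 0.6, or a one-sided test, was meant, state that and give the reason.

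A figure for 24 evaluable participants (65% power for a change of 0.5; detectable change 0.60) may be added, but only labelled as a complete-case sensitivity scenario.

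The cost is a change of wording and a slightly less favourable stated figure. No further participants, visits or analyses are needed.

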### Statistical methods

Quantitative analyses will include within-group analyses of variance (ANOVAs) and non-parametric assessments between time points, for mentees and mentors separately. Multiple imputation procedures that utilise the expectation-maximisation (EM) algorithm with bootstrap estimates of standard errors will be used for missing data. Using the six-stage approach described by Braun and Clarke [35], thematic analysis will be undertaken to identify key themes in the qualitative data.

## Discussion

Eating disorders are disabling and often long-term conditions. The efficacy of available treatments is limited, resulting in high relapse rates and significant morbidity and mortality. The current trial aims to assess the efficacy and feasibility of a peer mentor program (as a supplement to standard treatment) for patients with eating disorders, in terms of improvements in both eating disorder symptomatology and quality of life, as well as relapse rates. A unique aspect of this research is to assess the impact of this program on mentors to identify the positive and/or negative impact that engaging with current eating disorder patients has on someone who has recovered from an eating disorder. This study will assess any adverse effects on mentees or mentors and glean information that will inform refinement of the intervention for a full-scale randomised controlled trial. The findings of this pilot program will inform larger randomised controlled trials assessing the efficacy of peer mentoring for individuals with eating disorders, by providing preliminary data on the need of the program (i.e. participant flow and retention rate, and the magnitude of the outcomes to be clinically significant).

### Trial status

Protocol version: 1.5, 12/12/2017. Date recruitment began: 20/01/2017. Estimated date recruitment will be completed: 30/06/2018.

### Dissemination of results

Findings will be published in peer-reviewed journals and presented in national and international conferences. No restrictions are placed on the publication of results. Author eligibility will be based on ICMJE criteria.

## Abbreviations

ANOVA: Analysis of variance
AQoL: Assessment of Quality of Life
BDQ: Brief Disability Questionnaire
BETRS: Body Image and Eating Disorders Treatment and Recovery Service
DASS-21: Depression Anxiety Stress Scale
DSM-5: Diagnostic and Statistical Manual for Mental Disorders
EDE-Q: Eating Disorder Examination Questionnaire
EDV: Eating Disorders Victoria
TMC: The Melbourne Clinic
